### Follow-up

Outcomes will be recorded at 14 days and three and six months after intervention (Table 2). Information to be collected will include clinical and hemodynamic status, laboratory tests (complete blood cell count, liver function test, prothrombin time International Normalized Ratio), ankle–brachial index (ABI), adverse events, and other health problems and computed tomography angiography (CTA).

**Table 2 Tab2:** Assessment schedule

Visit date	Visit 1	Visit 2	Visit 3	Visit 4
	0 day	14 days	3 months	6 months
Demographic data	○			
Medical/surgical history	○			
Concomitant diseases	○		○	○
Concomitant medication/treatment	○		○	○
Physical examination (vital signs)	○	○	○	○
Laboratory results (CBC, LFT, PT INR)	○	○	○	○
ABI	○	○	○	○
CTA or angiography	○			○
Adverse events		○	○	○

*CBC* complete blood cell count, *LFT* liver function test, *PT* prothrombin time International Normalized Ratio, *ABI* ankle–brachial index, *CTA* computed tomography angiography

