### Outcome measures

The primary outcome of the study is the restenosis rate, defined as > 50% luminal reduction by CTA or catheter angiography in the six-month follow-up period. Secondary outcomes include target lesion revascularization, major bleeding, ipsilateral major amputation, all-cause mortality, and all adverse events that take place in those six months.

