### Adverse effects

Recording of serious adverse events (SAE) will conform to the Good Clinical Practice standards and the Research Governance Framework 2005. Analysis of safety-related data will be performed with respect to frequency of SAE including all-cause death, stroke, myocardial infarction (MI), or revascularization, early thrombosis, major bleeding, and major amputation. MI is defined as symptoms of ischemia with electrocardiographic changes compatible with MI or cardiac markers at least twice the upper normal limit [13]. Stroke is defined as brain hemorrhage, transient ischemic attack, or cerebral infarction with focal or global neurological deficits with signs or symptoms confirmed by a neurologist on the basis of neuroimaging results [14]. Major bleeding is defined as a need for a blood transfusion (≥ 2 packs), surgical intervention, or hypotension requiring inotropic support (hemoglobin reduction ≥ 2 g/dL). GUSTO bleeding criteria will be used [15]. Major amputation as a SAE is define as unplanned above-the-ankle amputation. Early thrombosis is defined as any event that occurs within 30 days after EVT. SAEs must be reported by the attending physician to the principal investigator within 24 h after the SAE becomes known.

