### Statistical considerations

The aim of this study is to show the non-inferiority of sarpogrelate to clopidogrel in preventing restenosis. From the previous literature, we found a six-month restenosis rate in patients on clopidogrel of 11% and a six-month restenosis rate in patients on sarpogrelate of 6% following EVT for FP artery intervention (7). The targeted significance level is 2.5%; the sarpogrelate group proportion is assumed to be 16% under the null hypothesis of inferiority. A sample size of 136 in each group will achieve 80% power to detect a non-inferiority margin difference between the group proportions of 5% assuming a dropout rate of 10%.

Randomization will be done by an independent statistical core at the Medical Research Collaborating Center of Seoul National University Hospital. Permuted block randomization will be used with blocks of sizes 4 or 6 to ensure a balance between the two treatment groups. We will use SAS 9.4 (SAS institute Inc., Cary, NC, USA) for sequence generation, which is to be stratified for: (1) presence of occlusion within the index lesion; (2) use of stent; (3) TASC classification “A or B” vs. “C or D;” and (4) presence of critical limb ischemia. Allocation of treatment will be done via a web-based randomization system, which returns the treatment group after the input of a participant’s study ID and the inclusion/exclusion criteria.

Characteristics of participants will be summarized using mean and standard deviation for continuous variables and frequency and percentage for categorical variables. A two-sided 95% confidence interval for a difference in restenosis rate between the two treatment groups will be calculated; then, whether the upper limit of the confidence interval should fall within the pre-determined margin of non-inferiority will be evaluated to prove the non-inferiority of sarpogrelate to clopidogrel. The conclusion will be based on the result of intention-to-treat analysis, while the per-protocol analysis result will be provided by utilizing data on patients with treatment compliance > 80%. Among the secondary outcomes, adverse events will be analyzed using chi-squared tests or Fisher’s exact tests as appropriate. Major bleeding, ipsilateral amputation, revascularization, and all-cause mortality will be compared using log-rank tests and survival curves constructed using Kaplan–Meier methods.

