Significance tests will be two-sided. A *P* value of < 0.05 according to SAS will be taken to indicate a statistically significant difference between the groups. SAS 9.4 (SAS institute Inc., Cary, NC, USA) will be used for data analysis.

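### Kaplan-Meier curves for revascularization, amputation and bleeding ignore precluding death (and, for revascularization, amputation); they slightly overstate incidence, and the revascularization log-rank can favour an arm where amputation replaces revascularization.

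*Protocol article*

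**What the plan says.** The method is in the protocol article, Statistical considerations: "Major bleeding, ipsilateral amputation, revascularization, and all-cause mortality will be compared using log-rank tests and survival curves constructed using Kaplan–Meier methods". The endpoints come from Outcome measures: "Secondary outcomes include target lesion revascularization, major bleeding, ipsilateral major amputation, all-cause mortality, and all adverse events that take place in those six months". Amputation and death are therefore outcomes in their own right, and no composite of limb events is defined.

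Three other places bear on the point:

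- Follow-up sets a short horizon: "Outcomes will be recorded at 14 days and three and six months after intervention".
- Adverse effects describes the amputation concerned: "Major amputation as a SAE is define as unplanned above-the-ankle amputation".
- The stratification list in Statistical considerations includes critical limb ischemia, so patients for whom amputation is a realistic outcome are enrolled.

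The article does not mention censoring or competing events. The full protocol and the statistical analysis plan are not shown.

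**The concern.** A patient who dies can no longer have a revascularization, an amputation or a major bleed. A patient who has lost the leg above the ankle will rarely have the femoro-popliteal lesion treated again. In a single-endpoint Kaplan-Meier analysis such a patient is normally censored, which means that the curve treats the patient as still able to have the event later.

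Two different things follow:

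- **Description.** One minus Kaplan-Meier no longer estimates the proportion of patients who have the event by six months. It is too high.
- **Comparison.** Amputation and repeat revascularization can be alternative ends of the same failing limb. If one arm has more failures ending in amputation, its revascularization count falls for a bad reason. Read alone, the log-rank test would then look favourable to that arm.

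Revascularization is the first-listed secondary outcome. A reader would naturally set it beside an imaging-based non-inferiority result.

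**Working it through.** **Inputs.** From the protocol article: the named method, the six-month horizon, 136 patients per group, and two-sided tests at 0.05. The article gives no rate for revascularization, amputation or death, so every such rate below is an assumption.

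**1. The plan's own figure.** The article's only design number is the sample size for the primary outcome. On the restenosis-free scale (0.89 clopidogrel, 0.94 sarpogrelate, margin 0.05, one-sided 0.025, power 0.80):

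n = (1.96 + 0.8416)² × (0.89×0.11 + 0.94×0.06) / (0.05 + 0.05)² = 7.849 × 0.1543 / 0.01 = 121.1, so 122. Then 122/0.90 = 135.6, so 136.

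This matches the article, and nothing below enters it.

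**2. Overstatement of incidence.** Assume constant hazards over six months, λ for revascularization and δ for death.

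- Cumulative incidence: λ/(λ+δ) × [1 − exp(−(λ+δ))]
- One minus Kaplan-Meier with deaths censored: 1 − exp(−λ)

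True incidence 10%, deaths 5%: λ+δ = −ln(0.85) = 0.1625; λ = 0.1625 × 0.10/0.15 = 0.1083; one minus Kaplan-Meier = 10.3%.

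True incidence 10%, deaths 10%: λ+δ = −ln(0.80) = 0.2231; λ = 0.1116; one minus Kaplan-Meier = 10.6%.

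Over a wider range (one minus Kaplan-Meier of 5% to 15%, competing-event risk of 2% to 15%), the gap runs from 0.05 points (5.00% against 4.95%) to 1.1 points (15.0% against 13.9%). It is larger in the arm with more competing events.

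**3. Log-rank test, competing events independent of limb failure.** Simulation with 136 per arm, 4,000 runs, and the same 10% revascularization risk in both arms:

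| Competing events | Favours arm with fewer | Favours arm with more |
|---|---|---|
| 2% vs 6% | 2.6% | 3.1% |
| 3% vs 10% | 2.7% | 2.4% |

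The nominal value is 2.5% per side. There is no tilt.

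**4. Log-rank test, amputation replacing revascularization.** Total limb failure is equal in both arms, and a share of failures ends in amputation. With failure risk F and amputation risk A, one minus Kaplan-Meier for revascularization is 1 − (1−F)^(1−A/F). For example, F = 10% and A = 5% give 1 − 0.9^0.5 = 5.1%. Simulated, again with 136 per arm and 4,000 runs:

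| Limb failure | Amputation | One minus Kaplan-Meier | Cumulative incidence | Log-rank favours high-amputation arm |
|---|---|---|---|---|
| 10% | 1% vs 3% | 9.1% vs 7.1% | 9.1% vs 7.0% | 8.4% |
| 10% | 1% vs 5% | 9.1% vs 5.1% | 9.0% vs 5.0% | 23.8% |
| 15% | 1% vs 5% | 14.1% vs 10.3% | 14.0% vs 10.0% | 15.2% |

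The test is not malfunctioning here: revascularization really is rarer in that arm. The error lies in reading this as a better limb outcome. Cumulative incidence shows the same gap, so changing the curve alone does not remove it. A composite of the two events does, because its hazard is equal in both arms by construction.

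**5. Would the separate amputation test show the trade-off?** It depends on the counts.

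- *Large contrast.* Suppose 8 revascularizations and 6 amputations against 14 and 0, out of 136 each. Revascularization is 5.9% vs 10.3%: chi-squared = 2×9/11 + 2×9/125 = 1.78, p about 0.18. Limb failures are 14 vs 14. Amputation 6 vs 0 has Fisher p = 2 × C(136,6)/C(272,6), about 0.03. The planned amputation comparison would flag the harm.
- *Smaller contrasts.* Amputation of 3% vs 1% is about 4 vs 1 patients; treating each amputation as equally likely in either arm, p is about 2 × (5+1)/2⁵ = 0.38. For 5% vs 1%, about 7 vs 1, p is about 2 × (8+1)/2⁸ = 0.07. Neither reaches 0.05.

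**The case against.** The strongest reply is that the article never says these patients are censored, and that such rules commonly sit in the analysis plan, which is not shown. That is fair for the rule itself, and its absence is not the point here. What the article does fix is plain Kaplan-Meier for outcomes that death can preclude, and an analysis plan that follows the sentence inherits the problem.

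A reader might infer more than the documents support:

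- *That an arm losing more limbs is always credited with fewer revascularizations.* Step 3 shows that this is not so. The credit needs amputation to replace revascularization in limbs already failing, and the article has no figures on how often that happens. Deaths do not plausibly act this way. The overstatement of the curve works against the arm with more competing events.
- *That all four outcomes compete.* They do not. Death precludes the other three, and amputation largely precludes revascularization. Bleeding and revascularization preclude nothing, and Kaplan-Meier is right for all-cause mortality.
- *That the log-rank test is invalid.* With competing events censored, it is a standard cause-specific comparison.
- *That the non-inferiority claim is at risk.* It rests on restenosis by imaging, and no section uses revascularization to support it.

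It is also true that amputation and mortality are compared separately, so a careful reader sees both sides. This protection is real for a large amputation difference and weak for a small one (step 5).

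**Conclusion.** The point holds as a minor one. The named curves are not the right estimate of six-month incidence for the three non-fatal outcomes. The error is about 0.3 to 0.6 percentage points at a true 10% with 5% to 10% deaths, and at most about 1.1 points over the range examined.

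The revascularization log-rank is valid for what it tests. Under substitution, it favours the high-amputation arm in 8% to 24% of simulated trials, against a nominal 2.5%, although total limb failure is equal. That result depends on assumed rates and on amputation standing in for revascularization. This is plausible in a population that includes critical limb ischemia, but the article does not quantify it. The primary conclusion and the 136 per group do not change.

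**What to change.** Amend Statistical considerations, or confirm that the full protocol or analysis plan already does so, along these lines:

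- Show each non-fatal outcome as cumulative incidence (Aalen-Johansen). Death is the competing event for major bleeding and amputation; death and ipsilateral major amputation are the competing events for revascularization.
- Keep Kaplan-Meier for all-cause mortality.
- Keep the listed log-rank tests, described as cause-specific comparisons.
- Add one supportive log-rank test of target lesion revascularization or ipsilateral major amputation, whichever comes first, with its components tabulated beside it. It supplements the listed outcomes and does not replace them.

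Both parts are needed. Cumulative incidence corrects the curves, and only the composite deals with substitution. The cost is small: the component events are already secondary outcomes, no visit is added, and the only downside is one more derived outcome. The article reports recruitment as ongoing, so at that stage the change could be specified before results are known.

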### Ethical approval

This study follows the principles of the Helsinki Declaration and all patients will provide written informed consent prior to participation. Participation can be withdrawn at any time without any negative consequences concerning current or future medical treatment. Study approval was given by the Institutional Review Board of Seoul National University Hospital (IRB No. 1607-151-778).

## Discussion

This study is designed to present evidence of the suitability of antiplatelet agents after endovascular revascularization in patients with FP arterial disease.

Some patients who participate in this study may have multi-level disease, including inflow or outflow problems as well as FP lesions, which may need to be corrected simultaneously. In other words, the inclusion criteria are broad, which reflects the situation in clinical practice. We will stratify the data on occlusion of the index lesion, use of stents, TASC AB and CD, and critical limb ischemia, which will help to determine the use of antiplatelet agent.

To date, DAPT, which consists of aspirin and clopidogrel, is well documented in patients with PCI. ESC guidelines recommend DAPT for one month after EVT with a stent for PAD [16]. However, the optimal antiplatelet agent is still unclear in long-term cases. The role of antiplatelet agents may decline after EVT for PAD owing to the development of new technology and devices that has occurred over the past decade [17]. Alternatively, the use of stronger antiplatelet agents may be required owing to various forces in the femoral artery during exercise and more aggressive treatment.

In the CAPRIE study, aspirin alone was associated with a higher rate of ischemic events than was clopidogrel [18]. That emphasized the necessity of DAPT rather than aspirin alone. Especially for cases of MI, ischemic stroke, and symptomatic PAD, DAPT with clopidogrel was more effective than ASA alone [19]. On the other hand, CASPAR failed to demonstrate a benefit of DAPT (aspirin plus clopidogrel), reminding us of the need for a variety of independent studies on the use of antiplatelet agents in PAD [20].

In one study, sarpogrelate reduced the restenosis rate (4.6% vs. 28.6%) after six months of coronary stenting [21]. There are three inhibitory effects of sarpogrelate: anti-platelet aggregation and anti-vasoconstriction prevent the development of early thrombus and anti-vascular smooth muscle proliferation is expected to reduce in-stent restenosis [9]. In addition, to protect endothelial cells by dose-dependently reducing the ICAM-1 level in a hyperglycemic state, it may also improve long-term patency after EVT [22].

Considering that patients with PAD are at high risk for bleeding, sarpogrelate has the potential benefit of lower bleeding risk compared to clopidogrel [23, 24]. In Korea, the price of sarpogrelate is lower than that of clopidogrel, which can reduce medical expenses (US$0.92 vs. US$1.02 per one tablet). Such potential benefits of sarpogrelate may be a good alternative if it is not inferior to clopidogrel-based DAPT. In conclusion, the SAFE study is a multicenter randomized controlled trial designed to show non-inferiority in terms of the re-stenosis rate of SR sarpogrelate compared to clopidogrel for EVT for PAD in FP lesion patients. We hope to address these issues in the SAFE study.

### Trial status

Recruiting is ongoing.

## Abbreviations

ABI: Ankle–brachial index
CTA: Computed tomography angiography
CVD: Cardiovascular disease
DAPT: Dual antiplatelet therapy
EVT: Endovascular treatment
FP: Femoro-popliteal
PAD: Peripheral artery disease
PCI: Percutaneous coronary intervention
TASC: Transatlantic Inter-Society Consensus
